# Targeted gluteal exercise versus sham exercise on self-reported physical function for people with hip osteoarthritis (the GHOst trial – Gluteal exercise for Hip Osteoarthritis): a protocol for a randomised clinical trial

**DOI:** 10.1186/s13063-018-2873-3

**Published:** 2018-09-20

**Keywords:** Hip osteoarthritis, Exercise, Buttocks, Gluteal, Gait, Clinical trial

## Abstract

**Background:**

Clinical practice guidelines recommend exercise as the first line of management for hip osteoarthritis, yet high-quality evidence from Cochrane reviews suggest only slight benefits for pain and physical function; and no benefit on quality of life (low-quality evidence). However, the scope of physical impairments identified in people with hip osteoarthritis may not have been adequately addressed with targeted rehabilitation options in previous randomised controlled trials (RCTs). Potential targeted options include gait retraining to address spatio-temporal impairments in walking; motor control training to address deep gluteal (gluteus minimus) dysfunction; and progressive, high-intensity resistance exercises to address atrophy of the gluteal muscles. The aim of this study is to investigate the effect of a targeted gluteal rehabilitation programme that incorporates gait retraining, motor control and progressive, high-intensity resistance-strength training, to address physical activity levels and self-reported physical function in people with mild to moderate disability from hip osteoarthritis.

**Methods:**

Ninety people diagnosed with mild to moderately disabling hip osteoarthritis will be recruited and randomised to receive one of two exercise programmes (sham or GHOst programme). Interventions will be 12 weeks in duration, with weekly, supervised physiotherapy sessions, and daily home exercises. Both groups will receive standardised education. Outcomes will be assessed at baseline, 7 weeks, 13 weeks (primary time-point) and 25 weeks. The primary outcome will be self-reported physical function measured with the Western Ontario and McMaster Universities Osteoarthritis Index (WOMAC). Secondary outcomes include physical activity measured with a tri-axial accelerometer, physical function tests, self-reported physical activity, isometric hip-muscle strength tests, hip-related patient-reported outcome measures, pain thoughts and depressive symptoms, quality of life, global rating of change, gluteal-muscle activity (electromyography (EMG)) and gluteal-muscle size and adiposity (magnetic resonance imaging (MRI)).

**Discussion:**

This will be the first study to compare a targeted gluteal rehabilitation programme to a sham exercise programme. The targeted GHOst programme includes exercises designed to address gait impairments as well as gluteal-muscle atrophy and dysfunction.

**Trial registration:**

Australian New Zealand Clinical Trials Registry, ID: ACTRN12617000970347. Registered retrospectively on 5 July 2017. Protocol version 3.0.

**Electronic supplementary material:**

The online version of this article (10.1186/s13063-018-2873-3) contains supplementary material, which is available to authorized users.

## Background

Osteoarthritis is a chronic, debilitating condition affecting many people worldwide. In 2016, approximately 4% of the global population had a diagnosis of osteoarthritis, with the prevalence reaching 9% in countries such as the United States, Germany and Canada [1]. Osteoarthritis typically presents in the weight-bearing joints of the lower limb such the hip and knee [2]. Symptoms in people with hip osteoarthritis usually deteriorate slowly [3], and this likely contributes to a reduction in physical function [4, 5] when undertaking simple activities such as walking. The symptoms and reduction in physical activity are thought to contribute to elevated Body Mass Index (BMI), weakness, stiffness, psychological distress, poorer quality of life [6], and greater personal and societal burden [7, 8].

Clinical practice guidelines recommend exercise and education as first-line management for osteoarthritis of the hip or knee [9–13]. The ultimate goal of exercise participation in people with osteoarthritis is to improve symptoms, physical function and quality of life. Theoretically, the improvements obtained with exercise are achieved by addressing bio-physiological (e.g. muscle strength, joint stability, cartilage integrity) and psychosocial impairments present in this patient group [4, 14–18]. A Cochrane review and meta-analysis concluded that there is moderate- to high-quality evidence that exercise has moderate benefits for pain and physical function, and slight benefits for quality of life in people with *knee* osteoarthritis [19]. However, exercise interventions for those with *hip* osteoarthritis appear to be less efficacious. High-quality evidence from a Cochrane review and meta-analysis suggests that exercise has only slight benefits for pain and physical function in people with hip osteoarthritis [20]; and no improvement in quality of life (low-quality evidence) [20]. A more recent, high-quality randomised controlled trial (RCT) supplements these findings to suggest that exercise combined with manual therapy is no better than a sham intervention (turned-off ultrasound) for improving pain and physical function in this patient group [21]. It is possible that the principles of exercise training programmes (frequency, intensity, type, duration and progression) have not been optimised to target the specific impairments associated with hip osteoarthritis, and these training principles are an important consideration for clinical prescription and future research [20, 22, 23].

Targeting specific impairments might be important to optimise outcomes of rehabilitation for people with hip osteoarthritis. Peak hip-abductor isometric strength, and hip-adduction moment during gait (a surrogate measure of hip-abductor strength) are significantly associated with pain while walking in people with hip osteoarthritis [24]. Furthermore, hip-abductor muscle atrophy is present in those with hip osteoarthritis, and this is associated with radiological and clinical severity [25, 26]. The use of progressive, high-intensity resistance-strength training for the hip abductors may potentially have a significant impact on symptoms during functional tasks like walking, and ultimately affect physical function and quality of life. There are, however, no studies that have investigated high-intensity resistance-strength training in this population [14, 20, 21]. In addition, individuals with symptomatic hip pathology present with biomechanical [27] and spatio-temporal [28] gait impairments that could potentially be addressed with rehabilitation. For example, reduced peak hip extension during gait is evident in early hip pathology [29] as well as established hip osteoarthritis [27, 30]. It has been theorised [31, 32] that loss of terminal hip extension reduces the stimulus of the deep anterior hip muscles (e.g. gluteus minimus (GMin)) to contract [33]. Weak or inefficient anterior hip muscles may consequently leave the anterior-superior hip joint vulnerable to further shearing, injury and degeneration [34, 35]. Indeed, GMin atrophy is present during end-stage hip osteoarthritis [26, 36], with a particular susceptibility of anterior GMin [37], and persists following hip surgery [38, 39]. It is, therefore, important to consider gait retraining and motor control strategies to correct for these biomechanical and muscle impairments.

Gait retraining has been recommended in recent clinical guidelines for the management of hip osteoarthritis [11]; however, this is based on weak evidence including expert opinion. There are currently no studies that include gait retraining during rehabilitation in people with hip osteoarthritis. Clearly, the scope of rehabilitation options for targeting specific impairments in people with hip osteoarthritis has not been fully explored. Potential options include, high-intensity resistance-strength training, gait retraining and motor control strategies targeting muscle segments (e.g. GMin anterior) that are known to atrophy in this population [37].

Using a parallel RCT design, the aim of this study is to compare a targeted gluteal rehabilitation programme that incorporates gait retraining, motor control and progressive, high-intensity resistance-strength training, to a sham exercise intervention for addressing self-reported physical function in people with mild to moderately disabling hip osteoarthritis.

## Methods

This study will be reported according to the Consolidated Standards of Reporting Trials (CONSORT) 2010 guidelines [40] and the protocol developed according to Standard Protocol Items: Recommendation for Interventional Trials (SPIRIT) (Additional file 1) [41, 42]. The study design and protocol follows the OARSI clinical trials recommendations for the conduct of clinical trials for hip osteoarthritis as set out in Lane et al. [43]. This study will compare the effect of a 12-week, targeted, physiotherapy-supervised gluteal exercise programme, with a 12-week physiotherapy-supervised, sham exercise programme in people with hip osteoarthritis. The trial has been registered on the Australian New Zealand Clinical Trials Registry (ACTRN12617000970347) with a Universal Trial Number (UTN) U1111–1192-1408. Where appropriate, approval for trial modifications will be sought by the relevant ethics committee and updated on the ANZCTR. The study will take place in three Australian cities (Bendigo, Melbourne, Brisbane) and one New Zealand city (Dunedin) involving physiotherapy clinics across the public and private sectors.

### Ethical approval and consent

This trial adheres to the principles of the Declaration of Helsinki, and has received ethical approval from the Bendigo Health Care Group Human Research Ethics Committee (HREC/17/BHCG/3); La Trobe University HREC; The University of Queensland (20,170,001,541/HREC/17/BHCG/3) and Otago University HDEC (17/STH/205). All participants will provide informed, written consent before commencing the study.

### Design

This is a two-arm, assessor- and participant-blind, parallel, randomised clinical trial, with a 12-week intervention period and outcomes measured at baseline, 7 weeks, 13 weeks and 25 weeks (Fig. 1).

**Fig. 1 Fig1:**
[figure not shown]
Flow of participants through the study

### Participants

#### Recruitment

Potential participants with hip osteoarthritis will be recruited via local print media and through advertising flyers distributed through participating health providers and community notice boards. Further advertising through social media and radio and online advertising service will be conducted. Interested volunteers will contact chief investigators ([name]) at one of the four participating sites via telephone or email and will be screened (by telephone) for eligibility.

#### Eligibility

The inclusion criteria are as follows: mild to moderate disability from idiopathic (primary) hip osteoarthritis in accordance with the American College of Rheumatology [44] as defined by:(i)Aged > 35 years(ii)Pain in the hip or groin for more than 3 months(iii)Pain intensity over the past week of ≥ 30 or higher on a 100-mm visual analogue scale (VAS) during functional tasks like walking, climbing stairs or climbing in/out of a car(iv)Radiographic confirmation of hip osteoarthritis with a Kellgren-Lawrence score ≥ 2 [45](v)Mild to moderate disability indicated by:Oxford Hip Score of 25–45 indicating mild to moderate disability [46, 47]Still able to reciprocally ascend and descend 10 stairs unaided [48]Still able to safely walk one city block, andAble to jog 5 m(vi)Satisfactory completion of an adult pre-exercise screening tool (https://www.essa.org.au/wp-content/uploads/2011/09/Screen-tool-version-v1.1.pdf)

Exclusion:(i)Other musculoskeletal lower limb or back conditions requiring assessment or treatment in the last 6 months(ii)Primary complaint of gluteal tendinopathy (clinical diagnosis), low back pain or referred back pain (Additional files 2 and 3)(iii)History of hip trauma or surgery on either the affected or unaffected side(iv)Known knee joint pathology that may impact on the ability to perform the intervention or reduced knee range of motion (< 90° flexion)(v)Corticosteroid use (oral or intra-articular) in the past 3 months(vi)Neurological impairment or condition affecting lower-limb function(vii)Conditions or factors affecting ability to take part in the exercise intervention, e.g. unavailable for a 12-week intervention period, routine use of gait aids, uncontrolled hypertension, or morbid obesity (Body Mass Index > 40)(viii)Systemic inflammatory disease (e.g. rheumatoid arthritis)(ix)Unable to write, read or comprehend English

In addition, participants at one site (Bendigo; total of 30 participants) will be asked to complete a magnetic resonance imaging (MRI) scan and undergo fine-wire electromyography (EMG) of the GMin and gluteus medius (GMed) muscles. These volunteers will be ineligible to participate if they have any contraindication to fine-wire EMG (e.g. fear of needles, taking blood-thinning medication) or MRI (e.g. pacemaker, claustrophobia).

### Study procedure

#### Telephone screening

Interested volunteers will initially be screened over the telephone by one of the chief investigators at each of the four study sites. Telephone screening will aim to assess and exclude potential participants who do not fulfil the eligibility criteria. Reasons for exclusion at this stage include, but are not limited to; a clear diagnosis other than hip osteoarthritis; inability to complete a 12-week intervention programme at a trial physiotherapy clinic; Oxford Hip Score outside the range of 25–45; unable to walk a city block, ascend/ descend a set of 10 stairs, or jog 5 m; pain < 30 mm on a VAS during functional tasks; routine use of gait aids.

#### Physiotherapy assessment

Potential participants who satisfy the initial telephone screening will be invited to attend a physiotherapy screening examination. This screening session will include a physical examination to exclude gluteal tendinopathy and lumbar spine pain as the primary source of hip pain; and to exclude knee pathology that may affect their ability to complete the exercise programme. Screening for gluteal tendinopathy (clinical diagnosis) will be completed using the following protocol (Additional file 2): (1) tenderness to palpation over the greater trochanter (high sensitivity [85.7 (66.4–95.3)] suggesting that a negative test would rule out the condition [49]), in combination with (2) pain reproduction with the flexion, abduction, external rotation test (FABER) [49, 50] and (3) one other clinical test associated with gluteal tendinopathy (resisted external de-rotation test, resisted abduction test, single-leg stance test (30 s) [49, 51]. Lumbar spine referral as a primary source of pain will be screened by the following criteria (Additional file 3): (1) reproduction of hip symptoms with repeated lumbar flexion, lumber extension, or quadrant testing and (2) reproduction of hip symptoms with passive straight leg raise to 45° hip flexion. The physiotherapist will also assess passive knee range of motion to ensure > 90° of pain-free movement in order to screen for serious knee pathology. If potential participants satisfy the remaining eligibility criteria, they will once again be instructed on the nature of the study, offered the opportunity to ask questions about the study, and invited to provide written, informed consent (Additional file 4).

#### Assessor blinding

All outcome measures will be assessed by a research assistant at each site who will be blind to participant group allocation. Participants will be instructed not to divulge any aspect of their intervention to the research assistant conducting follow-up assessments.

#### Participant blinding

Participants will be blinded to group allocation (sham or Gluteal exercise for Hip Osteoarthritis (GHOst) protocol). They will be advised that they have an equal chance of being allocated to the either protocol. Participants will also be blind to the study hypothesis, so they are unaware which of the interventions is ‘active’.

#### Physiotherapy blinding

It is not possible to blind the trial physiotherapists to group allocation. Trial physiotherapists will, however, not be involved in assessment outcome measures.

### Interventions

Participants will be randomly allocated to the GHOst intervention or the sham intervention. Both groups will receive standardised education for hip osteoarthritis delivered by a trial physiotherapist and supplemented with handouts. Education will focus on an understanding of the condition and general advice on physical activity. Participants will be asked to refrain from other active, supervised (e.g. from a health professional) non-pharmacological rehabilitation for their hip osteoarthritis for the duration of the trial.

Both groups (GHOst and sham) will receive once weekly, supervised physiotherapy sessions and a self-managed exercise programme over 12 weeks. The self-managed home exercise programme will consist of the same exercises prescribed during the supervised sessions. The initial physiotherapy session will be a one-to-one session for 1 h, incorporating education and exercises, delivered by the trial physiotherapist. The additional supervised sessions will be 30 min and conducted in an individual or group setting (i.e. one to three participants per session), based on availability of participants and scheduling of the trial physiotherapist. Participants will only attend group sessions with other participants who have been randomised to the same intervention. Whether participants attend group or individual sessions will be documented by the trial physiotherapist, and accounted for as a potential covariate in statistical analysis. Daily exercise adherence (frequency and duration) will be monitored with an exercise diary [52].

#### GHOst protocol: targeted gluteal intervention

The GHOst protocol is composed of three phases. Gait retraining, motor control (anterior hip stability) and pelvic stability with global, high-intensity resistance-strengthening. Exercises within each phase are progressed based on quality (judged by the trial physiotherapist), symptoms (pain not exceeding 5/10 on a numerical pain rating scale) and ability to complete the relevant dose.

##### Gait retraining

The aim of the gait retraining component is to normalise, prevent or minimise gait-related impairments and symptoms that are commonly associated with hip osteoarthritis [28, 53]. This includes pain with walking, reductions in stride length, decreased peak hip extension range of motion, decreased cadence, decreased gait speed, gait asymmetry and increased pelvic obliquity at push-off [27, 28, 53]. Techniques will be prescribed by the trial physiotherapist to normalise stride length and asymmetry. These include, but are not limited to, auditory cueing [54], backwards walking [55, 56] and instructions on techniques that may reduce pain when walking; for example, ‘push more with your feet when you walk’ [57, 58].

##### Motor control (anterior hip stability)

The second phase of the GHOst intervention aims to promote the function of the anterior hip muscles (particularly anterior GMin) using targeted, functional progressions of a split squat and bridge exercise. GMin appears to have a particular vulnerability to atrophy in people with hip pain [26, 32, 37], especially the anterior portion [32, 37–39]. This phase will, therefore, have a focus on anterior GMin muscle recruitment using elastic exercise bands to promote active hip internal rotation [33, 59] in functional, closed-chain positions. Participants will be asked to complete up to five repetitions of 30-s holds for isometric exercises; three sets of 12 to 20 repetitions for dynamic exercises.

##### Pelvic stability with global strengthening

The third phase of the GHOst intervention aims to improve pelvic stability and overall lower-limb and trunk strength and function. These exercises progress from isometric hip hitching [60–63], through to high-intensity resistance-strength training of multiple muscle groups (e.g. double-leg squat and dead-lift) with the aid of Theraband and power-bands (Aussie Strength, Smithfield, NSW Australia) to achieve the required intensity. The high-intensity resistance exercise component of this phase will use the Borg CR10 scale [64–67], asking participants to exercise at a ‘heavy load’ equivalent to Borg ≥ 5 to < 7. This intensity has been validated for use with hip exercises [66]. For the high-intensity resistance exercises, participants will be asked to perform three sets of 6 to 10 repetitions.

### Sham exercise protocol

The sham protocol is similar to that being used in a RCT in people with greater trochanteric pain syndrome [61]. The sham programme differs to the GHOst protocol in that it is not aimed at strengthening the gluteal muscles, but includes generalised lower-limb, low-intensity resistance exercise. Participants are guided through sham gluteal, quadriceps’ and calf exercises, predominantly in a seated position (unloaded).

### Physiotherapy treatment fidelity

To maximise physiotherapy treatment integrity, all trial physiotherapists will have at least 2 years of musculoskeletal clinical physiotherapy experience, and will receive mandatory standardised training (1 day) before being assigned their first participant. Training will cover interventions to be implemented (sham and GHOst), the education to be delivered to participants and trial reporting (e.g. clinical note taking and adverse events). Training will incorporate techniques described by Main et al. [68] for training therapists to implement clinical trial interventions; including trainer-led teaching, role play, group discussions and ongoing clinical mentoring and support throughout the trial.

In addition to training, trial physiotherapists will receive a trial manual that includes an illustrative guide to exercise progressions. Trial physiotherapists will also document the exercises prescribed, adherence, use of pain medication or non-steroidal anti-inflammatory drugs (NSAIDS), and adverse events at each treatment session on standardised recording forms.

### Baseline assessments

Demographic details including age, gender, height and weight will be recorded.

### Outcome measures

The outcome measures are in accordance with those recommended by OARSI for clinical trials on people with hip osteoarthritis [43, 69].

#### Primary outcome measure

##### Self-reported physical function

Self-reported physical function as assessed by the physical function subscale of the Western Ontario and McMaster Universities Osteoarthritis (WOMAC) Index Likert version 3.1 [70].

The physical function subscale of the WOMAC is a 17-item 5-point Likert scale ranging from 0 to 68 with higher scores indicating greater dysfunction. It is a valid and reliable self-administered tool [71] that is recommended for clinical trials in hip osteoarthritis [43], with a minimal clinically important difference of 6 units [72].

#### Secondary outcome measures

##### Physical activity accelerometry

A tri-axial accelerometer (Link; Actigraph Corp., Pensacola, FL, USA) will be used as the objective, reliable measure of physical activity [73]. Participants will attach the accelerometer to a waistband anterior to the right hip for collection of movement data, at an acquisition frequency of 100 Hz. Participants will remove the accelerometers when sleeping (to avoid sleep disturbance) and bathing (due to the lack of water-proofing) [74]. The accelerometer will be worn for a 7-day period in week 0 (prior to commencing the intervention) and week 12 (last week of the intervention).

Output data will be downloaded and analysed in 1-min epoch intervals using the manufacturer’s software (Actilife ver.6; Actigraph Corp., Pensacola, FL, USA). The total time that the participant undertook sedentary, light, moderate and vigorous physical activity will be determined for each valid wear day using previously recognised algorithms [75]. The accumulated total of minutes of moderate and vigorous activity for the week will be summed to determine weekly total moderate to vigorous physical activity (MVPA, min/week) [76].

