### Sample size and power analysis

The minimal clinically important difference for the WOMAC is 6 physical function units [72]. Using data from the sham intervention of a previous RCT in people with hip osteoarthritis [21], the standard deviation (SD) of change in the WOMAC over 13 weeks is 9.2 units, assuming a baseline to follow-up correlation of 0.60. A total sample size of 76 participants (38 per group) is required to detect a clinically important difference between sham and intervention groups, with a power of 80% and an alpha of 0.05. A clinically important difference of 6 units between groups, assuming a within-group SD of 9.2 units equates to a moderate to large effect size (0.65). To account for potential drop-outs similar to those reported in previous studies [21] we will recruit 90 participants (45 per group).

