### Statistical analysis

Statistical analysis will be using intention-to-treat principles and on a per-protocol basis. Data analysed will focus on detecting the between-group treatment and within-group treatment effects (with effect sizes and 95% confidence intervals) at each of the follow-up time-points. A linear mixed model will be used for the primary analysis of the changes in the WOMAC due to its advantages in modelling the influence of nonlinear, individual differences over time. Adjustments will be made for the respective baseline outcome measures, as well as age, sex and BMI; and adjustments for other baseline variables that have evidence of imbalances between groups (e.g. radiographic severity). The secondary outcomes will be assessed using *t* tests or Mann-Whitney *U* tests, adjusting for baseline differences if required. The Global Rating of Change Scale will be dichotomised to define ‘success’ as those with a score of ‘moderately better’ to ‘very much better’ (i.e. + 3 or more). A generalised mixed model (adjusted for baseline differences and covariates) will be used to assess differences in the proportion of ‘successes’ between groups over each time-point.

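### Weekly MVPA is summed over valid wear days without normalising for their number, so an incomplete wear week scores on average only k/7 of the true weekly total

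*Protocol article*

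**What the plan says.** The Protocol article, under Physical activity accelerometry, sets a seven-day wear period in week 0, before the intervention starts, and another in week 12, its last week. Time spent sedentary and in light, moderate and vigorous activity "will be determined for each valid wear day using previously recognised algorithms". For the weekly outcome, "The accumulated total of minutes of moderate and vigorous activity for the week will be summed", and the result is labelled a weekly total in minutes per week. The section does not define a valid day, set a minimum number of them, require all seven, or average or rescale by their number.

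Under Statistical analysis, "The secondary outcomes will be assessed using" t tests or Mann-Whitney U tests, with baseline adjustment where needed. Neither valid days nor wear time is named as an adjustment.

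**The concern.** Referring to valid wear days implies that some days may be invalid. An invalid day supplies no minutes, yet the sum over the remaining days still carries the label of a full week. The score then depends on two things: how active the participant was and how many days counted.

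Accelerometry is the trial's only objective measure of physical activity; the other measure, the IPAQ short form, relies on recall. The outcome is measured in two separate weeks, so a shift in wear between them goes straight into the change score. Adjusting for baseline MVPA does not restore days lost in week 12.

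**Working it through.** **The plan's own figures.** The article gives no MVPA mean, SD or wear-compliance figure, so there is none to reproduce here. Its one computed design figure, under Sample size and power analysis, concerns WOMAC physical function: 6/9.2 = 0.652, for which a two-sided t-based calculation at 80% power and alpha 0.05 gives 37.9, so 38 per group as stated. Nothing below depends on it.

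**Inputs.** Seven planned days per wear period, minutes counted on valid days, and a plain sum over the week come from Physical activity accelerometry. Mean daily MVPA, m, is an assumption, shown at 10, 20 and 30 min/day. Unworn days are assumed to resemble worn ones.

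**Step 1: level.** With k valid days the stated rule gives k × m, against a true weekly total of 7 × m. The relative error is k/7 − 1.

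| Valid days k | Error | m = 10 | m = 20 | m = 30 |
|---|---|---|---|---|
| 7 | 0% | 70 | 140 | 210 |
| 6 | −14.3% | 60 | 120 | 180 |
| 5 | −28.6% | 50 | 100 | 150 |
| 4 | −42.9% | 40 | 80 | 120 |

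The last three columns are the recorded score in min/week.

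**Step 2: change within a participant.** Take 7 valid days in week 0 and 5 in week 12.
- No true change: 5m − 7m = −2m, a false change of −20, −40 or −60 min/week at m = 10, 20 or 30.
- A true rise of 20% per day: the rule gives 5 × 1.2m − 7m = −m, so −10, −20 or −30. The true change is 7 × 0.2m = 1.4m, so +14, +28 or +42. The sign is reversed.

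**Step 3: comparison between arms.** With equal daily activity in both arms, the false difference is the difference in mean valid days times m.
- 6.5 against 6.0 days: 0.5m = 5, 10 or 15 min/week, which is 0.5/7 = 7.1% of the true weekly total.
- 6.5 against 5.0 days: 1.5m = 15, 30 or 45 min/week.
- Equal valid days: zero. The ratio between arms is then intact, although a true difference in minutes shrinks with the level.

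**Step 4: after normalising.** (k × m / k) × 7 = 7m for any k. At m = 20, participants with 4, 5, 6 or 7 valid days all score 140 min/week.

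**The case against.** The strongest reply is that the article is silent on incomplete weeks rather than wrong about them. For a complete week a plain sum is correct. The definition of a valid day, a minimum-days rule and any rescaling are details that a condensed article commonly leaves to the full protocol, the analysis plan or the cited methods, none of which is shown. This stands for the valid-day definition and the minimum-days rule, whose absence is not counted against the plan. It does not dispose of the aggregation step, because the article states that step itself and without qualification. An average per valid day set out elsewhere would contradict the sentence, not elaborate it.

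Three stronger readings are tempting and are not supported:

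- **Everyone with an incomplete week is under-scored.** A participant with no MVPA on the invalid days loses nothing. If seven valid days were required, the participant would be excluded instead. The k/7 factor is an average.
- **Routine removal makes days invalid.** The article says "Participants will remove the accelerometers when sleeping" and when bathing. That is planned waking wear, and nothing in the text says it invalidates a day.
- **A false difference between arms is to be expected.** This needs wear to differ by arm. Participant blinding describes participants as unaware of allocation and hypothesis, Interventions gives both arms the same weekly supervised contact, and the wear instructions are common to all. The article does not suggest differential wear.

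**Conclusion.** The point holds as a badly fixed derivation of one secondary outcome. As written, weekly MVPA is low on average by 14%, 29% and 43% at 6, 5 and 4 valid days, assuming unworn days resemble worn ones. These percentages do not depend on the assumed daily MVPA; the figures in minutes do. The consequences are a lower level, extra noise in the outcome, and change scores that can be wrong in sign for a participant whose valid days fall between the two weeks. How many participants would be affected cannot be said, since no wear figure is given. A spurious difference between arms is conditional on unequal valid days. The primary outcome, its analysis and the sample size are untouched.

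**What to change.** Define the outcome as mean MVPA minutes per valid day, multiplied by 7 if it is to be reported per week, for participants who meet a pre-specified minimum number of valid days in the wear period. Apply the same rule in week 0 and week 12. It would help to report the number of valid days by arm and time-point, so that a reader can see whether wear was similar.

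The cost is one line in the derivation, on data already collected. The small downside is that missing days are taken to resemble worn ones; the present sum in effect counts them as zero, which is less plausible. If the full protocol or analysis plan already normalises in this way, the sentence under Physical activity accelerometry should be corrected to match.
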